## Abstract

**Background:**

It is well recognised that the adoption and longer term adherence to physical activity by adults to reduce the risk of chronic disease is a challenge. Interventions, such as group and home based physical activity programs, have been widely reported upon. However few studies have directly compared these interventions over the longer term to determine their adherence and effectiveness. Participant preference for home based or group interventions is important. Some evidence suggests that home based physical activity programs are preferred by middle aged adults and provide better long term physical activity adherence. Physiotherapists may also be useful in increasing physical activity adherence, with limited research on their impact.

**Methods:**

'Physical Activity at Home' is a 2 year pragmatic randomised control trial, with a non-randomised comparison to group exercise. Middle-aged adults not interested in, or unable to attend, a group exercise program will be targeted. Sedentary community dwelling 50-65 year olds with no serious medical conditions or functional impairments will be recruited via two mail outs using the Australian federal electoral roll. The first mail out will invite participants to a 6 month community group exercise program. The second mail out will be sent to those not interested in the group exercise program inviting them to take part in a home based intervention. Eligible home based participants will be randomised into a 6 month physiotherapy-led home based physical activity program or usual care. Outcome measures will be taken at baseline, 6, 12, 18 and 24 months. The primary outcome is physical activity adherence via exercise diaries. Secondary outcomes include the Active Australia Survey, accelerometry, aerobic capacity (step test), quality of life (SF-12v2), blood pressure, waist circumference, waist-to-hip ratio and body mass index. Costs will be recorded prospectively and qualitative data will be collected.

**Discussion:**

The planned 18 month follow-up post intervention will provide an indication of the effectiveness of the group and home based interventions in terms of adherence to physical activity, health benefits and cost. If the physiotherapy-led home based physical activity program is successful it could provide an alternative option for physical activity program delivery across a number of settings.

**Trial registration:**

Australia and New Zealand Clinical Trials Register (ANZCTR): ACTRN12611000890932

## Background

The incidence of chronic disease dramatically increases in middle age. Conditions such as cardiovascular disease, type II diabetes and cancer are mostly experienced by people in the middle or older age groups [1]. A major risk factor for chronic disease is physical inactivity [2]. By improving physical activity levels towards the recommended level in this age group, it can have a significant effect on their quality of life and future health [3,4].

In 2004-5 the Australian Bureau of Statistics reported approximately 70% of Australians aged 15 years or more were classified as sedentary or having low levels of physical activity [5]. To increase our physical activity levels a number of health promotion strategies have been employed, such as General Practitioner advice, mass media campaigns, tailored information for communities and community programs targeting groups or individuals [6]. Yet physical activity interventions in middle and older age adults have reported difficulties with the adoption and adherence to physical activity with a number of barriers identified [7,8].

Physiotherapy-led home based programs may be an alternative option to increase the adoption and long term adherence to physical activity. As primary health care providers physiotherapists are well placed to promote physical activity in both the private and public sector for primary prevention of chronic disease [9]. Physiotherapists prescribe exercise for a wide range of conditions and comorbidities utilising a strong background in disease pathologies and body systems. They are well equipped to provide a thorough assessment, individually tailored prescription of exercise and appropriate counselling to achieve an increase in physical activity [10,11]. However, primary prevention of chronic disease via physical activity programs appears to be under utilised in physiotherapy [12]. Shirley [9] found that physiotherapists were far more likely to incorporate physical activity advice into a regular treatment session for a condition rather than a non-treatment one-on-one or group physical activity consultation. Further investigation of physical activity promotion and physiotherapy is needed to determine its impact.

One of the barriers to physical activity adoption may be that individuals prefer to exercise on their own. There is some evidence that a large number of community dwelling individuals may not be interested in group exercise but would undertake exercise on their own in their local area if they had access to appropriate exercise information and or supports. Wilcox reports from a large community survey conducted in the USA that 69% of middle-aged and 67% of older adults preferred to exercise on their own with some instruction rather than in a group exercise class [13]. Yardley reports that 41% of respondents in a large survey conducted in the UK over the age of 54 would not attend group sessions for falls prevention [14]. Some people may also not be suited to groups, particularly those that are lonely and depressed and have decreased cognition [8].

Community based physical activity studies have found that longer term retention of participants within an intervention is difficult [15,16]. Jancey [8] in a 6-month community physical activity intervention for older adults found that participants lost to attrition (35%) came from areas of lower socioeconomic status, were overweight and less physically active, had lower walking self-efficacy scores and higher loneliness scores. Participants reported that they were unable to continue with the physical activity program due to work and travel commitments, and group times being unsuitable. Attrition was not related to age, relationship status, level of education, or gender.

Participant choice and suitability of physical activity programs needs to be considered in order to increase the adoption and adherence to physical activity. A number of physical activity promotion strategies are group or centre based. Home based physical activity programs have been investigated although many appear not to be completely home based, involving some group component or attendance at a centre for assessments [17,18]. To our knowledge there are no known trials reported in the literature of targeted interventions for those individuals who do not wish to take part in group programs.

There is also some evidence that home based programs provide better long term adherence to exercise than centre based programs [19]. This Cochrane review included only 6 studies on home versus centre based physical activity programs in adults older than 50 years. The largest and highest quality rating study in this review found that there was a significantly higher adherence rate to physical activity in the home based program compared with the centre based program, especially in the long term [20]. King [20] reported that at 12 months following the initiation of group and home based interventions, the group intervention had an approximately 50% adherence to exercise, while the home based intervention had a 70% adherence to exercise. Recommendations from this review included investigation of reasons for better adherence in home based programs and exploring the cost-effectiveness of centre and home based programs.

Individual home based physical activity programs with telephone support can be a viable strategy for home based physical activity program provision [18,21]. Telephone counselling has been found to be effective in promoting physical activity in middle-aged and older adults in both healthy and chronic illness samples and has the potential for being a lower cost and more convenient alternative to face-to-face contact [21,22].

Therefore by targeting middle aged adults, where the number of chronic diseases begins to increase noticeably, with a physiotherapy-led home based physical activity program it may increase the adoption and adherence to physical activity over the longer term. By comparing the home based intervention with telephone support to a standard community group exercise program and usual care we will determine the health benefits, longer term adherence to physical activity and the cost effectiveness of delivering such programs.

We hypothesize that:

1. There are a large number of individuals in the community aged 50-65 years who are not interested in group exercise, a commonly used method to increase the population's level of physical activity in the community.

2. A proportion of this group would commence exercising if an alternative method of increasing physical activity was available, such as a home based approach.

3. The home based physical activity program would produce health benefits equivalent to those seen in the group based exercise program for sedentary adults 50-65 years old.

4. Those that commence the home based physical activity program are more likely to continue with an increase in physical activity in the long term, as compared to a group based program.

5. A home based approach to increasing physical activity with minimal support is more cost effective than a group based intervention, taking into consideration long term physical activity adherence.

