### Sample size

The sample size for this study was based on the study by King [20] cited earlier, reporting a 20% difference in adherence to physical activity between a group and home based intervention at 12 months. Assuming a standard deviation of 35% based on this study and a dropout rate of 25% with a statistical power of 0.8, the sample size needed for each group is 64.

Previous community physical activity intervention studies using various recruitment methods, including utilisation of the AEC federal electoral roll, report a recruitment rate of 10-20% [20,24]. Therefore it was estimated that approximately 2000 letters need to be sent in the first mail out to recruit a suitable sample size.

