### Statistical methods

Data will be analyzed according to group assignments, regardless of how many participants actually complete the study, the intent-to-treat principle. A maximum of four attempts will be made to contact participants that did not comply with the intervention protocols so outcome measures can be obtained, making the analysis more complete [37].

An intention-to-treat analysis may result in an underestimate of treatment effect, making it harder to find a significant difference [37]. Therefore data will be analyzed using both intention-to-treat and on-protocol analyses to determine if the two methods yield the same or different results. This justifies the allowance of a 25% drop-out rate.

Significance level will be set at *p *< 0.05. All analyses will be conducted using SPSS version 18.0.

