### Randomised control trial

The primary analysis for the RCT will use repeated measures analysis of covariance (ANCOVA). All analyses will be adjusted for baseline values. Additional covariates to be considered include: gender, age and employment status, an ordinal measurement.

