### Other analyses

A subsidiary comparison with the group exercise program will use the ANCOVA as described above, with the addition of the third intervention group.

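### Hypothesis 3 claims equivalent health benefits for the home and group programs, but the only analysis described for that comparison is a test of difference, which cannot support the claim

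*Protocol article*

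**What the plan says.** Hypothesis 3 (protocol article, Background) is worded as a claim of equivalence between the two active programs: "The home based physical activity program would produce health benefits equivalent to those seen in the group based exercise program".

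For the analysis, the section on the randomised trial specifies repeated measures ANCOVA adjusted for baseline values. The section Other analyses extends it to the group arm: "A subsidiary comparison with the group exercise program will use the ANCOVA as described above, with the addition of the third intervention group". Under Statistical methods the significance threshold is p < 0.05, and the stated worry about intention-to-treat is framed in terms of detecting differences: "An intention-to-treat analysis may result in an underestimate of treatment effect, making it harder to find a significant difference".

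The Sample size section builds on an earlier study "reporting a 20% difference in adherence to physical activity between a group and home based intervention at 12 months". The other inputs are given as follows: "Assuming a standard deviation of 35% based on this study and a dropout rate of 25% with a statistical power of 0.8". The result is 64 per group. The Discussion describes this number as giving power for a significant difference in the main outcome measure, which is adherence.

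The Design section calls the group arm non-randomised. The Discussion lists the lack of randomisation as a limitation on attributing outcomes to treatment across the three groups.

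**The concern.** The hypothesis and the test point in opposite directions. An ANCOVA at p < 0.05 takes no difference as its null. Rejecting that null is evidence of a difference; failing to reject it is not evidence of equivalence, because it may only reflect imprecision. Neither outcome of the stated analysis can support hypothesis 3.

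This goes beyond detail that an article leaves to a fuller document. The article itself names the hypothesis, the model, the threshold and the basis of the sample size for this comparison, and these do not fit together.

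At stake is how a null result would be reported. If p > 0.05 came to be taken as support for hypothesis 3, then dropout and noisy measurement would make the claim easier to reach. The Discussion presents the home program as a possible alternative way of delivering physical activity programs, so the wording of that conclusion matters.

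**Working it through.** **1. What the sample size is for.** Inputs from the Sample size section: difference 20 points, SD 35 points, power 0.80, dropout 25%. The threshold of 0.05 is from Statistical methods. Sidedness is not stated, so two-sided is assumed.

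n per arm = 2 × [SD × (z₀.₉₇₅ + z₀.₈₀) / difference]² = 2 × [35 × (1.960 + 0.842) / 20]² = 48.07

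Allowing for dropout: 48.07 / 0.75 = 64.1, which matches the stated 64. A one-sided test would give 38, or 51 after dropout, which does not match. So 64 is the size for a two-sided test of a difference in adherence. It contains no equivalence margin and no health outcome.

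**2. Precision available for a health outcome.** The article gives no SD for these outcomes, so the scale is SD units. Evaluable per arm: 64 × 0.75 = 48.

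- Standard error, unadjusted: √(2/48) = 0.204 SD.
- 95% CI half-width: 1.96 × 0.204 = 0.40 SD.

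**3. Chance of a non-significant result when a real difference exists** (two-sided 5% t-test, unadjusted, one outcome):

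| True difference | 48 per arm | 64 per arm (no dropout) |
|---|---|---|
| 0.2 SD | 84% | 80% |
| 0.3 SD | 69% | 61% |
| 0.4 SD | 51% | 39% |
| 0.5 SD | 32% | 20% |

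**4. Allowing for baseline adjustment.** The plan adjusts for baseline, which multiplies the standard error by √(1 − r²), where r is the correlation between baseline and follow-up. The article gives no r; 0.5 to 0.7 is assumed. The factors are √0.75 = 0.866 and √0.51 = 0.714. With 48 per arm:

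| | r = 0 | r = 0.5 | r = 0.7 |
|---|---|---|---|
| 95% CI half-width | 0.40 SD | 0.35 SD | 0.29 SD |
| Non-significant at a true 0.3 SD | 69% | 61% | 47% |
| Margin at which two one-sided 5% tests have 80% power (true difference 0) | 0.60 SD | 0.52 SD | 0.43 SD |

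The last row is (1.645 + 1.282) × standard error; for r = 0 it is 2.927 × 0.204 = 0.597.

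**5. What a formal equivalence test would need.** With two one-sided 5% tests, 80% power, a true difference of 0 and no adjustment, n per arm = 2 × (2.927 / margin)². This gives 191 evaluable (255 with 25% dropout) for a margin of 0.3 SD, 108 (144) for 0.4 SD and 69 (92) for 0.5 SD. With 48 evaluable, power is 0% at 0.3 SD, 25% at 0.4 SD and 58% at 0.5 SD. These margins are illustrative, since the article states none.

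**The case against.** A reader might infer that the plan intends to declare equivalence whenever p > 0.05. The article does not say so: it gives a model and a threshold, and no decision rule for hypothesis 3. An ANCOVA also yields adjusted differences with confidence intervals, and an interval rule could be applied to the same model. This objection stands, and the point is limited accordingly: the stated analysis cannot support the hypothesis, and no other rule is given.

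A reader might also infer that a real disadvantage of the home program would usually be missed. That is true only for smaller differences. Unadjusted with 48 per arm, the chance of a non-significant result is about even at 0.4 SD and falls to 32% at 0.5 SD. Baseline adjustment lowers these figures, and combining four follow-up visits might lower them further. They also refer to a single outcome, whereas several health outcomes are measured.

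The absence of a margin or a designated health outcome is not in itself a fault, since an analysis plan not shown here may supply them. What remains is the mismatch between the stated hypothesis and the stated test. A margin set elsewhere would still need a decision rule different from the one in the article.

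Finally, the comparison is labelled subsidiary, the group arm is self-selected, and the Discussion acknowledges this. That lowers the severity. It also means that a confidence interval inside a margin would not by itself show that the programs are equivalent, because confounding could mask a difference.

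**Conclusion.** The point holds at moderate severity. Hypothesis 3 asserts equivalence of health benefits, the only analysis described for it tests for a difference, and the sample size was set for a difference in another outcome. As stated, the analysis cannot support the hypothesis.

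This conclusion follows from the text and does not depend on the numbers, which only show its practical size. At 48 evaluable per arm the data would leave differences of roughly 0.3 to 0.4 SD unresolved, and a true 0.3 SD deficit would be non-significant in about half to two thirds of trials (47% to 69%). These figures assume 25% dropout, a two-sided 5% level, one outcome at one time point, and a baseline correlation between 0 and 0.7.

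The randomised comparison of the home program with usual care is unaffected.

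**What to change.** Reword hypothesis 3 so that its aim is to estimate the baseline-adjusted home-minus-group difference in health outcomes with a 95% confidence interval. Add one sentence stating that a non-significant difference will not be read as equivalence. This is the better option here, because a formal equivalence claim between self-selected arms would remain open to confounding.

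If the word *equivalent* is kept, name the health outcome or outcomes for hypothesis 3 and justify a margin for each before data are seen. Require the 90% confidence interval of the adjusted difference (two one-sided 5% tests) to lie wholly within the margin, and qualify any conclusion for the non-random allocation. The calculations above suggest that the planned size would reach 80% power only for margins of about 0.43 to 0.60 SD, depending on the baseline correlation, and it may be hard to defend margins that wide.

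The cost of the first option is wording only, with no extra participants or visits. The trial may have to give up the word *equivalent*.

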## Methods

### Design

'Physical Activity at Home' is a 2 year, pragmatic, two arm randomised control trial (RCT) targeting middle-aged adults not interested in, or unable to attend, a group exercise program. Participants eligible for the home based intervention will be randomised, via computer generated numbers, to a physiotherapy-led home based physical activity program or usual care.

Comparison of the physiotherapy-led home based physical activity program and usual care to a non-randomised group exercise program will also be completed. The group exercise program has been included to replicate a standard community physical activity program for middle-aged adults. Using a quasi-experimental design the three interventions will be compared to determine the long term adherence to physical activity, health benefits and cost.

### Participants

To be eligible for this study, participants will be between 50 and 65 years old. Participants must be sedentary; that is, no participation in regular moderate or vigorous exercise or physical activity for 30 min 2 or more times a week for at least 6 months. They will have no serious medical conditions that could limit participation in moderate physical activity, such as unstable angina, uncontrolled hypertension, diagnosed or hospitalized with chest pain, heart attack or heart surgery in the past 6 months and no severe functional impairments due to multiple medical or psychiatric diseases. They will not be planning to move from the area within 2 years and only one person per household will be eligible. Participants will be English speaking and have appropriate cognitive skills to provide informed consent and actively engage in the physical activity program. Medical clearance screening will be undertaken using the Sports Medicine Australia (SMA) Pre-Exercise Screening System [23]. If the participant answers 'yes' to any of the SMA screening questions, they will be asked to attend their local medical officer to receive medical clearance before they can be included in the study.

### Recruitment

Recruitment to the 'Physical Activity at Home' study will take place between February and April 2011. Two mail outs will be conducted using the Australian Electoral Commission (AEC) federal electoral roll to target 50-65 year olds in six suburbs of the Australian Capital Territory (ACT). These suburbs were chosen due to their geographical proximity to a local YMCA. The first letter will ask for expressions of interest in joining a once weekly group exercise program at the local YMCA. The second letter will be sent to those not interested in the group exercise program inviting them to participate in a health project that will consist of either a 6 month physiotherapy-led home based physical activity program or the completion of a number of basic health measures in their homes giving them an indication of their fitness and health status. All individuals that respond to the mail outs will be screened via telephone. The flow of participants through the trial is illustrated in Figure 1.

**Figure 1 F1:**
[figure not shown]
**Flow of participants through the trial**.

### Intervention

(i) Home-based intervention

Assessments for the home based program in this study will be conducted in participant's homes eliminating a number of barriers to physical activity adoption as discussed earlier [24]. Participants will be encouraged to invite a support person to attend during their initial assessment. After baseline measures are completed motivational interviewing will be used to devise an individual physical activity program [25]. A physiotherapist will discuss type, frequency, intensity, duration, benefits, barriers, goals, self-monitoring and progression of physical activity, aiming to achieve 30 min of moderate intensity physical activity most days of the week. Participants will be contacted by a physiotherapist via phone providing advice and support 2 weeks after the initial assessment and then monthly over a 6 month period, a total of approximately 6 phone calls.

(ii) Usual Care

Participants randomised to usual care will be visited by the physiotherapist in their homes. Baseline measures for the study will be completed giving participants an indication of their fitness and health status. Participants will receive two brochures 'An active way to better health. National Physical Activity Guidelines for Adults' and 'Dietary Guidelines for Australian Adults' from the Department of Health and Ageing [26,27]. They will not receive any other advice or support for increasing exercise or physical activity levels.

(iii) Group exercise program

Participants in the group based program will attend the YMCA for their baseline measures. Baseline measures will be conducted by the same physiotherapist as the home based interventions. Participants will then have a choice of times for the group based exercise program which will be during business hours replicating similar programs and times offered in this community setting. These sessions will be run by a YMCA fitness instructor at the YMCA once a week, for 60 min, over 6 months. The exercise program will involve upper and lower body strengthening exercises, gross motor skill training and aerobic fitness training. The exercise specifics will be at the discretion of the YMCA fitness instructor, with no involvement from the physiotherapist, aiming to mimic 'usual practice'. Participants will be encouraged to increase their physical activity slowly and gradually in whichever way they prefer outside of the group sessions by the YMCA fitness instructors, aiming to achieve 30 min of moderate intensity physical activity most days of the week. An individual home based exercise program will not specifically be designed for this group.

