## Discussion

Over a 2 year period the 'Physical Activity at Home' study will test the effectiveness, in terms of long term physical activity adherence, health benefits and cost, of a physiotherapy-led home based physical activity program. Specifically it will target middle aged adults who are less likely to adopt and maintain physical activity, as they do not access the currently available community group exercise programs. With few studies reporting on the long term adherence to physical activity post intervention and no known studies reporting on targeted physical activity interventions for those not interested in group or centre based programs, if this program is successful it could allow more individuals to increase their physical activity levels towards that needed to achieve the associated health benefits.

One of the strengths of this trial is that the inclusion criteria are broad proposing that there is some benefit from physical activity for almost everyone [42]. The recruitment method also attempts to minimize self-selection and recruitment of highly motivated volunteers by using the electoral roll, allowing a more representative sample [24]. Phone coverage is widespread in Australia therefore recruitment and providing the home based intervention via this method should also limit selection bias. All measurements will be performed by the same person and the sample size to be recruited should provide adequate statistical power to detect a significant difference in the main outcome measure.

A limitation of this study is the lack of randomisation to the group and home based interventions limiting the ability to attribute outcomes to treatment for all three groups. There is also a lack of blinding, as the principal researcher will be conducting all assessments and providing the home based intervention. Another possible limitation is the type of personnel conducting the interventions is not standardised, that is, a physiotherapist as compared to a fitness instructor.

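### As the text reads, baseline is measured after randomisation by the unblinded physiotherapist who delivers the home programme, so baseline covariates can be affected by allocation and people who withdraw before the visit have no baseline.

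*Protocol article*

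**What the plan says.** All references are to the protocol article.

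- **Recruitment:** "All individuals that respond to the mail outs will be screened via telephone". The second letter tells recipients about both the home programme and the measurement-only alternative.
- **Design:** "Participants eligible for the home based intervention will be randomised, via computer generated numbers, to a physiotherapy-led home based physical activity program or usual care". No baseline visit is mentioned between screening and this step.
- **Intervention, usual care:** "Participants randomised to usual care will be visited by the physiotherapist in their homes. Baseline measures for the study will be completed".
- **Intervention, home-based:** "Participants will be encouraged to invite a support person to attend during their initial assessment". And then: "After baseline measures are completed motivational interviewing will be used to devise an individual physical activity program".
- **Discussion:** a lack of blinding is acknowledged, because "the principal researcher will be conducting all assessments and providing the home based intervention".
- **Randomised control trial (analysis):** "All analyses will be adjusted for baseline values". The model is a repeated measures ANCOVA, and Statistical methods commits to intention to treat.

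**The concern.** Adjusting for baseline is safe when allocation cannot have influenced the baseline value. If the arm is known before the measurement, that protection goes. A participant told to expect a programme may answer an activity survey differently, or try harder or less hard on a step test, than one told to expect brochures. An assessor who will go on to treat one arm may coach or record differently. ANCOVA treats the resulting difference between arms as chance imbalance and corrects for it, which puts a bias into the treatment effect. The direction cannot be predicted.

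The second risk is loss of people. Someone who withdraws after learning their allocation but before the visit is randomised yet has no baseline. A baseline-adjusted model fitted to complete cases leaves that person out. If such withdrawals are commoner in one arm, the groups analysed are no longer the groups randomised.

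Both risks concern only the two randomised arms. The group exercise programme is not randomised.

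**Working it through.** **1. Order of events.** Eligibility is settled by telephone (Recruitment). Eligible people are randomised (Design). Those described as already randomised to usual care are then visited and measured (Intervention). In the home arm, baseline comes directly before the motivational interview at the initial assessment. No sentence places baseline before allocation or says that allocation is withheld until baseline is complete.

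**2. Who knows the arm.**
- Assessor: one person measures everyone and delivers the home programme. If allocation precedes the visit, that person knows it. This is well supported.
- Participant: inferred from two facts. The letter names both options, and the encouragement to bring a support person, which has to be given before the visit, appears under the home-based heading only.

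**3. Which measures are exposed.** The Active Australia Survey and SF-12v2 are self-reported, and the 2-minute step test depends on effort. The accelerometer is worn for 7 days over the same period as the survey, so behaviour in that week could also respond to a known allocation. BMI is the least vulnerable. The primary outcome is diary adherence over the 2 years, and no diary period before the intervention is described, so it is unclear which baseline value would be its covariate.

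**4. The plan's own figure.** The plan gives no number on this point. Its sample size serves only to set the scale. With a difference of 20 points, SD 35, power 0.8 and two-sided 5% (sidedness assumed):

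n = 2 × [35 × (1.960 + 0.842) / 20]² = 48.07 per arm; 48.07 / 0.75 = 64.1.

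The stated 64 is reproduced, with about 48 per arm analysed. The concern does not alter it.

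**5. Size of covariate bias (assumed inputs).** Let d be the shift in measured baseline in one arm, in SD units, and r the baseline-to-follow-up slope on standardised scales. The documents give neither. Then, in absolute size,

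bias = r × d; SE ≈ √(2/48) × √(1 − r²).

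This takes a single follow-up and ignores the small increase in SE from the imbalance itself. Each cell gives the bias in SD and, in brackets, the actual two-sided error rate at a nominal 5%.

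| r | d = 0.1 | d = 0.2 | d = 0.3 |
|---|---|---|---|
| 0.3 | 0.03 (5.3%) | 0.06 (6.1%) | 0.09 (7.5%) |
| 0.5 | 0.05 (5.9%) | 0.10 (8.7%) | 0.15 (13.6%) |
| 0.7 | 0.07 (7.7%) | 0.14 (16.1%) | 0.21 (30.2%) |

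**6. Loss before baseline (assumed inputs).** If a fraction w of one arm withdraws between allocation and visit, 64 × w people have no baseline. That is 0 at w = 0, 6.4 at w = 0.10, and 16 if the plan's whole 25% dropout allowance fell there. The documents give no value for w.

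**The case against.** The case against has real force on several points.

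- **The order is a reading of the prose.** Figure 1 could settle it, and the phrase about those randomised to usual care could be just an arm label in a section organised by arm. An article may also leave allocation procedure to the full protocol. This stands as a limit on certainty. It does not remove the point: the prose has one natural reading, and nothing in the text contradicts it.
- **Participant knowledge is not stated.** The article uses the term home based for both randomised arms in places (Abstract, Design), so the support-person sentence might cover every home assessment. A reader might infer that participants certainly know their arm at baseline. The text makes this probable and no more.
- **The blinding limitation is disclosed.** A reader might infer that the protocol overlooks unblinded measurement at baseline. It does not: the Discussion statement covers every assessment, and Outcome measures lists baseline among them. What can be said is that at baseline, unlike at follow-up, the problem is avoidable with the same staff.
- **The primary outcome is not shown to be biased through its covariate.** It has no described diary baseline, and the measures most at risk are secondary. Loss of people before baseline could still affect any baseline-adjusted analysis, the primary one included.
- **The magnitudes are assumptions.** Nor does a baseline shift carry over in full, because the slope attenuates it. The handling of missing baseline values may also be set out in an analysis plan that is not shown.

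**Conclusion.** The point holds in limited form. As written, baseline in the randomised arms follows allocation and is taken by the unblinded person who delivers one of the treatments. Covariates based on self-report or effort can therefore be affected by allocation, and early withdrawals may fall out of the baseline-adjusted intention-to-treat comparison.

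Bias is possible and has not been demonstrated. Under the assumed ranges it runs from negligible (0.03 SD, error rate 5.3%) to serious (0.21 SD, error rate about 30%), and the documents give no basis for choosing a value within that range. The conclusion rests on the prose order being correct, and a look at Figure 1 or the full protocol would confirm or overturn it. The change is worth making because the risk is avoidable at little cost.

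**What to change.** - Complete all visit-based baseline measures before allocation is disclosed. Then reveal a concealed, computer-generated allocation at the end of those measures in the same visit, for example from a sealed envelope. The motivational interview or the brochures can follow directly.
- Extend the support-person invitation to both randomised arms. Issuing it only after allocation would not work with a same-visit reveal, because that person is meant to attend that visit.
- Where the accelerometer can be supplied beforehand, collect its baseline week before disclosure too. Otherwise state that the baseline accelerometer week follows allocation. Requiring it first in every case would need device delivery or a second visit, neither of which the article describes.
- If baseline-first is already the intended order, correct the usual-care wording in the Intervention section to say so.

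The cost is small: each visit must be prepared for either arm, and no extra staff are needed.
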